#### Observation, examination, and evaluation items at each visit (Table 2)

**Table 2 Tab2:**
[figure not shown]

[figure not shown]
Study schedule for observation, inspection, and evaluation

● Represents the examination and assessment items to be performed at each visit

^#^1: Acceptable range of the required tests at Day 1, as indicated by 〇, are 14 days. Treatment using test device starts at Day 1

^#^2: Consent from the participants must be obtained at least 28 days before the start of the study

^#^3: Participants recall and assess the level of pain experienced over the past 4 weeks at each visit

^#^4: Data collected through the electronic Patient Reported Outcome (ePRO) system will be used for the assessment

^#^5: The participant diary will start recording from the date of consent. Recordings until the day before Day1 will be on paper diary, while from Day1 onwards, record will be collected by ePRO

BMI: body mass index; NRS: Numeric rating Scale; B&B: Biberoglu and Behrman; EHP-30: Endometriosis Health Profile-30; EQ-5D: EuroQol 5-Dimension

Treatment using the test device will commence on Day 1, and the NRS, B&B, EHP-30, and EQ-5D scores will also be collected on Day 1. NRS scores will be assessed by participants recalling their endometriosis-related pelvic pain over the 4 weeks prior to the visit. The following items will be assessed at the visits in weeks 4, 8, 12, 16, and 20 after the initiation of the trial:Height and BMIVital signs, including systolic and diastolic blood pressure and body temperatureSubjective and objective pain symptomsAverage NRS score for the 4 weeks preceding the visitMaximum and average NRS scores during menstruation within the 4 weeks preceding the visitMaximum and average NRS scores for periods other than menstruation within the 4 weeks preceding the visitB&B, EHP-30 score, and EQ-5D scoresUltrasonography to identify ovarian endometriotic cysts and other endometriotic lesions. Ovarian endometriotic cysts will be evaluated using the same measurements as the screening examinationOccurrence of adverse eventsConcomitant medications and therapies.

In the event of discontinuation of the device by a participant, the reasons for discontinuation will be included in addition to the observation items mentioned above.

#### Participant diary

Paper-based records and ePRO will be used to collect daily data, including the presence or absence of menstruation, number of devices used, quantity of device pads used, NRS scores (reflecting maximum pain in the preceding 24 h before input), utilization of analgesics, and the occurrence of adverse events.

### Assignment of interventions and blinding

After obtaining consent, eligible participants confirmed through screening tests will be randomized. The randomization at a 1:1 ratio will be conducted at the data center to achieve central registration and minimize bias. For the random allocation, the minimization method will be employed, adjusting for the trial facility and the presence or absence of low dose estrogen-progestin and progestin treatment within each group. The principal investigator will initiate protocol treatments for participants determined to be ‘eligible’ according to the randomization results. Therefore, the trial participants and principal investigator will be blinded to interventions after assignment.

### Statistical analysis

The baseline characteristics for participants in each group will be summarized, presenting frequencies and percentages for categorical variables and summary statistics (number of cases, mean, standard deviation, and minimum, median, and maximum values) for continuous variables. For group comparisons, Pearson’s Chi-squared test will be used for categorical variables, Fisher’s exact test will be applied for cells with an expected frequency < 5% and > 20%, and the t-test or Mann–Whitney U test will be used for continuous variables.

A two-tailed 5% significance level will be used. A two-tailed Student’s t-test will assess the primary outcome (null hypothesis: the difference in NRS score change between the treatment and control groups equals zero; alternative hypothesis: the difference in NRS score change between the treatment and control groups is not equal to zero). Rejection of the null hypothesis and adoption of the alternative hypothesis will occur if p < 0.05.

Additionally, an analysis of variance with the allocation factor as a fixed effect will be performed as a sensitivity analysis, and the Wilcoxon rank-sum test will be performed for a non-parametric analysis. The secondary endpoint analysis will be similar to the primary endpoint analysis. For the safety endpoint, frequencies and proportions of the patients with adverse events will be presented for each group. Exact two-sided 95% confidence intervals, assuming a binomial distribution, will be calculated for each group, and Fisher’s exact test will be used to compare groups. All statistical analyses will be performed using SAS version 9.4 or higher (SAS Institute Japan Ltd, Tokyo).

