### Outcome measures

#### Primary outcome

The primary outcome of this study is the change in the NRS score for endometriosis-related pain collected at each visit and at the end of the double-blind period (after 16 weeks) compared with the baseline score at the start of treatment.

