### Sample size calculation

The sample size calculation is based on the findings of a randomized controlled trial assessing the effect of the AT-02, a prototype of the AT-04, in patients with fibromyalgia [9]. Anticipated placebo effects of the sham device are approximately 14%. In previous open trials for dysmenorrhea, participants with NRS scores ≥ 6 before treatment initiation experienced a significant reduction in NRS scores by 1.73 as the total effect, encompassing the true effect and placebo effect. Assuming a true effect of 1.49 and attributing 14% as the placebo effect, the calculated placebo effect will be 0.24. The standard deviation of the actual device was approximately 1.8, and that of the sham device was approximately 0.3. Employing a two-sided non-paired t-test, the effect size was set to 0.969, alpha was set to 0.05, and power was set to 0.9. A sample size of 24 participants per group, totalling 48 participants, is required to achieve a conservative beta error. Considering potential dropouts, a sample size of 50 is deemed appropriate.

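### The unadjusted t-test on NRS change is a valid primary analysis, but it gives away precision by leaving out baseline NRS and the minimisation factors

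*Protocol article*

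**What the plan says.** All references are to the protocol article.

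- **Primary outcome:** the "change in the NRS score for endometriosis-related pain collected at each visit and at the end of the double-blind period (after 16 weeks"), measured against the score at the start of treatment.
- **Statistical analysis, primary test:** a two-tailed Student's "t-test will assess the primary outcome (null hypothesis: the difference in NRS score change between the treatment and control groups equals zero"). No covariate is named. On the error rate: "A two-tailed 5% significance level will be used". Secondary endpoints are to be analysed in a similar way.
- **Statistical analysis, sensitivity:** "an analysis of variance with the allocation factor as a fixed effect will be performed as a sensitivity analysis", and a Wilcoxon rank-sum test is added.
- **Assignment of interventions and blinding:** "the minimization method will be employed, adjusting for the trial facility and the presence or absence of low dose estrogen-progestin and progestin treatment". Baseline NRS is not one of the factors.
- **Observation items at each visit:** "the NRS, B&B, EHP-30, and EQ-5D scores will also be collected on Day 1", so the baseline covariate is already collected.
- **Sample size calculation:** a two-sided unpaired t-test for which "the effect size was set to 0.969, alpha was set to 0.05, and power was set to 0.9", leading to 24 per group.

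**The concern.** A change score does use baseline, but only by subtracting it with a fixed slope of 1. If the true slope of week-16 NRS on baseline NRS is below 1, subtraction over-corrects. The variance is then larger than it need be, and a chance imbalance in baseline pain carries into the estimate. With about 50 women, entry at an average NRS of 4 or more, and no balancing on baseline NRS, such an imbalance is quite possible. The article's own discussion of limitations expects relief to be weaker in women with moderate pain, so change is likely to depend on starting pain.

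The minimisation factors raise a second, smaller matter. When allocation is balanced on factors that predict the outcome and the analysis ignores them, the variation they explain stays in the error term. The standard error is then too large for the design.

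At stake is power in a small trial that allows only two participants for dropout (50 against 48).

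**Working it through.** **1. The plan's own figure.** The inputs come from Sample size calculation: "The standard deviation of the actual device was approximately 1.8, and that of the sham device was approximately 0.3", and effects of 1.49 and 0.24.

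- Pooled SD = √((1.8² + 0.3²)/2) = √1.665 = 1.290.
- Effect size = (1.49 − 0.24)/1.290 = 1.25/1.290 = 0.969, as stated.
- Noncentral t, two-sided 5%, 90% power: n = 23.4, rounded up to 24 per group, as stated. Power at 24 per group is 90.8%.

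The sizing therefore agrees with the unadjusted t-test. The inputs are taken here as the plan gives them.

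**2. Adjustment for baseline NRS.** Let ρ be the correlation of baseline with week-16 NRS, and k the baseline SD divided by the week-16 SD. Neither is in the documents, so both are assumed over a range. In units of the week-16 variance:

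- variance of the change score: 1 + k² − 2ρk
- residual variance after adjustment for baseline: 1 − ρ²
- ratio: (1 − ρ²)/(1 + k² − 2ρk), which becomes (1 + ρ)/2 when k = 1

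The slope on baseline is ρ/k, and the gain disappears when this equals 1. A k below 1 is plausible because entry at NRS 4 or more truncates the baseline distribution but not the week-16 distribution. Adjusted power uses the effect size 0.969/√ratio with 24 per arm. It ignores the one degree of freedom spent on the covariate.

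| k | ρ | Ratio | Effect size | Power |
|---|---|---|---|---|
| t-test | – | 1 | 0.969 | 90.8% |
| 1.0 | 0.3 | 0.65 | 1.202 | 98.3% |
| 1.0 | 0.5 | 0.75 | 1.119 | 96.7% |
| 1.0 | 0.7 | 0.85 | 1.051 | 94.6% |
| 0.7 | 0.3 | 0.91/1.07 = 0.85 | 1.051 | 94.6% |
| 0.7 | 0.5 | 0.75/0.79 = 0.95 | 0.995 | 92.1% |
| 0.7 | 0.7 | 0.51/0.51 = 1.00 | 0.969 | 90.8% |

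**3. Leaving out the minimisation factors.** Minimisation was simulated with 48 participants, eight facilities (the number named in Design and setting), a 50:50 hormonal factor, ρ = 0.5 and k = 1. The assignment probability was set at 0.8; the article gives none. There were 6,000 runs under the null. The variance explained was split equally between the two factors.

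| Variance of change explained by the factors | Type I error, t-test | Type I error, factors in the model |
|---|---|---|
| 0% | 4.7% | 4.7% |
| 10% | 4.6% | 5.2% |
| 20% | 3.6% | 5.2% |
| 30% | 2.6% | 5.2% |

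The simulation error at a true 5% is √(0.05 × 0.95/6000) = 0.3 points. The result at 10% therefore cannot be told apart from that at 0%.

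**4. The price of facility as a fixed effect.** Simulated power at effect size 0.969 (2,000 runs):

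| Model | Factors not prognostic | Factors explain 20% |
|---|---|---|
| t-test | 90.3% | 92.5% |
| Facility and hormonal factor | 88.3% | 94.6% |
| Baseline NRS only | 96.5% | 97.4% |
| Baseline NRS plus factors | 95.1% | 98.5% |

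Most of the gain comes from baseline NRS. Adding the fixed factors costs about 2 points (90.3 − 88.3) if they do not predict outcome.

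**The case against.** The strongest defence is that nothing here is wrong in the strict sense. A t-test on change is unbiased under randomisation, it is the test used for sizing, and the sizing reproduces. That stands: this is a weakness in efficiency, not an error.

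It is also fair that the gain from baseline depends on an SD ratio the documents do not give. If the baseline SD is 0.7 of the week-16 SD and ρ is 0.7, the gain is nil. This stands as a limit on the size. The direction is unaffected, since the ratio never exceeds 1.

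A reader might go further than the documents allow in four ways:

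- **That false positives are inflated.** The error runs the other way: the type I error falls below 5%, and only if facility or hormonal treatment is prognostic.
- **That the true type I error is about 3.9% or 2.8% when the factors explain 10% or 20% of the variance.** The formula 2(1 − Φ(1.96/√(1 − R²))) gives these values, but it assumes perfect balance. Simulated minimisation gives 4.6% and 3.6%.
- **That power starts at about 80%, or 65%.** Those figures put an SD of 1.8 in both arms, with a difference of 1.49 or 1.25. The plan's own inputs give about 91%. Whether a sham SD of 0.3 is credible is a separate question.
- **That the sensitivity ANOVA merely repeats the t-test.** This would be so if its allocation factor meant treatment group. Read beside the allocation section, it plausibly means the minimisation factors. On either reading it is not primary and names no baseline term.

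**Conclusion.** The point holds as a matter of precision. The primary analysis is valid and consistent with the sizing. But no stated analysis adjusts for baseline NRS, and the minimisation factors are outside the primary model.

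On the plan's inputs with 24 per arm, adjustment for baseline is worth between nothing and about 7 points of power (90.8% to 98.3%) over the range of ρ and k examined. The low end applies when the baseline SD is well below the week-16 SD and the correlation is high. Leaving out the minimisation factors makes the test mildly conservative if they explain some 20% of the variance or more, and makes no visible difference at 10%. These figures rest on assumed values for ρ, k, the variance explained and the assignment probability. The documents settle none of these.

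The change is worth making because the data are already collected and the cost is small.

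**What to change.** - Make the primary analysis an ANCOVA of the week-16 NRS change with terms for treatment, Day-1 NRS, hormonal treatment (yes/no) and facility. Pool small sites or fit facility as a random effect, because about eight fixed site effects are many for 50 women.
- Keep the unadjusted t-test and the Wilcoxon rank-sum test as sensitivity analyses.
- State that the allocation factor in the ANOVA sentence means the minimisation factors.

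**Cost.** The primary test is fixed in the protocol text, so both the protocol and the SAP need a wording change before unblinding. No new data, visits or participants are needed. The model spends a few degrees of freedom; with fixed facility effects and factors that are not prognostic, this came to about 2 points of power in the simulation. Pooling sites or using a random effect is meant to limit that loss.

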### Sample size calculation

The sample size calculation is based on the findings of a randomized controlled trial assessing the effect of the AT-02, a prototype of the AT-04, in patients with fibromyalgia [9]. Anticipated placebo effects of the sham device are approximately 14%. In previous open trials for dysmenorrhea, participants with NRS scores ≥ 6 before treatment initiation experienced a significant reduction in NRS scores by 1.73 as the total effect, encompassing the true effect and placebo effect. Assuming a true effect of 1.49 and attributing 14% as the placebo effect, the calculated placebo effect will be 0.24. The standard deviation of the actual device was approximately 1.8, and that of the sham device was approximately 0.3. Employing a two-sided non-paired t-test, the effect size was set to 0.969, alpha was set to 0.05, and power was set to 0.9. A sample size of 24 participants per group, totalling 48 participants, is required to achieve a conservative beta error. Considering potential dropouts, a sample size of 50 is deemed appropriate.

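### The stated effects and SDs give an effect size of 1.155, not the printed 0.969; the trial appears to be sized for an unstated difference of 1.25

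*Protocol article*

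**What the plan says.** Everything needed stands in the Sample size calculation section of the protocol article.

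- Placebo share: "Anticipated placebo effects of the sham device are approximately 14" per cent, taken from a fibromyalgia trial of the prototype device.
- Total effect: participants in previous open trials for dysmenorrhea "experienced a significant reduction in NRS scores by 1.73 as the total effect, encompassing the true effect and placebo effect".
- Split of that total: "Assuming a true effect of 1.49 and attributing 14% as the placebo effect, the calculated placebo effect will be 0.24".
- Variability: "The standard deviation of the actual device was approximately 1.8, and that of the sham device was approximately 0.3".
- Design parameters: "Employing a two-sided non-paired t-test, the effect size was set to 0.969, alpha was set to 0.05, and power was set to 0.9".
- Result: "A sample size of 24 participants per group, totalling 48 participants, is required to achieve a conservative beta error", then raised to 50 in total for dropouts.

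Allocation is 1:1 (Assignment of interventions and blinding). The primary analysis is a two-sided Student's t-test of the between-group difference in NRS change (Statistical analysis). The article does not show how 0.969 was obtained from the means and SDs.

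**The concern.** The difference that the primary test targets is the device-arm change minus the sham-arm change. If 1.73 already contains the placebo effect, and 1.49 is what remains once that effect is removed, then 1.49 is the expected between-group difference. The printed effect size does not correspond to 1.49 with the SDs given beside it.

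This paragraph is the article's only justification for the size of a phase III trial. A reader would take the trial to be powered at 90% for 1.49 points, when the printed effect size corresponds to 1.25. Anyone who later judges the result against the planned difference, or reviews the sample size, would start from the wrong target.

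**Working it through.** **Inputs** (all from Sample size calculation): total effect 1.73; placebo share 14%; true effect 1.49; placebo effect 0.24; SD 1.8 (device) and 0.3 (sham); two-sided alpha 0.05; power 0.90. Groups are of equal size.

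**1. From the printed effect size to the sample size.** For a two-sided, two-sample t-test (noncentral t) with d = 0.969, 90% power needs n = 23.4, so 24 per group. Power at 24 per group is 0.908. The plan's own figure is reproduced.

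**2. The split of the total effect.**
- 14% of 1.73 = 0.242, printed as 0.24.
- 1.73 - 0.24 = 1.49.
- 14% of 1.49 would be 0.209, so the 14% was applied to the total.

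The split is consistent, and 1.49 is already free of the placebo effect.

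**3. The between-group difference.** Device arm 1.49 + 0.24 = 1.73; sham arm 0.24; difference 1.73 - 0.24 = 1.49.

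**4. The effect size.**
- Common SD for equal groups: sqrt((1.8² + 0.3²)/2) = sqrt((3.24 + 0.09)/2) = 1.290.
- Effect size: 1.49/1.290 = 1.155, against 0.969 printed.

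**5. What does give 0.969?**

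| Difference | SD | Effect size |
|---|---|---|
| 1.49 - 0.24 = 1.25 | 1.290 | 0.9687, rounds to 0.969 |
| 1.49 | 1.290 | 1.155 |
| 1.73 | 1.290 | 1.341 |
| 1.49 × 0.86 | 1.290 | 0.993 |
| 1.73 | 1.8 | 0.961 |
| 1.49 | 1.8 | 0.828 |
| 1.73 | sqrt(1.8² - 0.3²) | 0.975 |

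Of the combinations tried, only the first gives the printed figure to three decimals, and it uses only numbers printed in the paragraph. To reach 0.969 from 1.49 the SD would have to be 1.49/0.969 = 1.538, which is not stated and is too far from 1.290 to be rounding.

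**6. Size of the mismatch** (two-sided t-test, alpha 0.05, stated SDs).

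| Difference | Effect size | n per group for 90% power | Power at 24 per group | Power at 25 per group (N = 50, no dropout) |
|---|---|---|---|---|
| 1.25 | 0.969 | 24 (48 in total) | 90.7% | 91.9% |
| 1.49 | 1.155 | 17 (34 in total) | 97.5% | 97.9% |

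The printed effect size is 16% below the one that the inputs imply (1.25/1.49 = 0.84). A Welch calculation, which allows for the unequal SDs, gives 18 per group and 97.0% power at 24 for a difference of 1.49, so the picture is the same.

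**The case against.** The strongest reply has four parts.

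*The printed design figures agree with each other.* This stands. A reader might infer that the effect size, the power and the sample size contradict one another. They do not: step 1 shows that 0.969, 90% and 24 per group fit together. The only broken link is from 1.49, 1.8 and 0.3 to 0.969.

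*The second subtraction is an inference.* This also stands. The article says that "the effect size was set to 0.969, alpha was set to 0.05, and power was set to 0.9" and gives no derivation. A match to three decimals makes a double subtraction very likely, but it cannot tell a slip from a deliberate discount. The Data Availability section refers to a detailed protocol in Japanese, and the derivation may be there. The remark about a conservative beta error leaves the intention open, but it concerns the type II error and neither states nor justifies a lower difference. None of this removes the mismatch between the figures that the article itself prints.

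*The mismatch is on the safe side.* On the stated inputs this is correct. A reader might infer that the trial is underpowered because of this point; the figures show the reverse.

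*The figures of 17 per group and 97.5% prove little.* A reader might infer from them that the trial is too large. They do not support that, because both depend on the sham SD of 0.3. As an illustration only, if both arms had an SD of 1.8 (an assumption), a difference of 1.49 would need 32 per group, and 24 per group would give about 80% power. Whether 0.3 is plausible is a separate question. Here the two figures serve only to measure the internal mismatch.

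**Conclusion.** The point holds as an error in a figure on which the sample size rests. The stated effects and SDs imply a between-group difference of 1.49 and an effect size of 1.155. The printed 0.969 corresponds to a difference of 1.25, most likely because the placebo effect of 0.24 was removed twice. The gap is 0.24 NRS points, or 16% of the effect size, and on the stated SDs it is the distance between 48 and 34 participants.

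The conclusion takes the article's own definitions of total, true and placebo effect as they stand, and uses a root-mean-square SD for equal groups. It does not extend to the step from 0.969 to 24 per group, which is correct, or to the primary test and its error rate, which are unaffected. That the cause was a slip rather than an intended discount remains an inference.

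**What to change.** Rewrite the paragraph in one of two ways.

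1. State the expected between-group difference as 1.49, correct the effect size (1.155 on the stated SDs), and give the power that follows at the planned N.
2. State that 1.25 was deliberately used as the design difference and give the reason. Keep 0.969, 90% and 24 per group, and make clear that 1.49 is not the difference the trial is sized for.

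In either case show the formula for the common SD, so that the effect size can be traced. Do not lower the number of participants because of this correction; the sham SD of 0.3 has to be examined on its own before any power figure is relied on. The cost is one corrected paragraph, with no change to the conduct of the trial.

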This study has some potential limitations that need consideration. First, it is challenging to determine the sole efficacy of AT-04 in treating endometriosis-related pain since all eligible women would have already been diagnosed with endometriosis, and most would have undergone treatment for endometriosis. Second, the NRS and HRQoL measurements may vary during the study period due to hormonal fluctuations associated with the menstrual cycle; this may impact the assessment of pain and quality of life. Finally, there is a possibility of insufficient pain relief by AT-04 because the study targets women with an NRS score ≥ 4 with moderate endometriosis-related pain. The effectiveness of pain relief may be comparatively weak in women with moderate pain. Furthermore, this study will be held in Japan. The relevance to other countries, race, ethnicities and cultures is another limitation.

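### The stated 90% power depends on an unjustified sham-arm SD of 0.3 and on an implied difference of 1.25 that does not match the stated true effect of 1.49

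*Protocol article*

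**What the plan says.** All the inputs are in the section Sample size calculation of the protocol article. It takes a total effect of 1.73 NRS points from open dysmenorrhea trials in women scoring 6 or more before treatment. It splits this into a true effect of 1.49 and a placebo effect of 0.24 (14%). On variability it says: "The standard deviation of the actual device was approximately 1.8, and that of the sham device was approximately 0.3". It continues: "Employing a two-sided non-paired t-test, the effect size was set to 0.969, alpha was set to 0.05, and power was set to 0.9". The result is 24 per group, which it says "is required to achieve a conservative beta error", and the total of 48 is raised to 50 for dropouts.

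Two other places bear on this. Under Statistical analysis, the primary test is a two-tailed Student's t-test on NRS change. The Discussion lists as a limitation that "the NRS and HRQoL measurements may vary during the study period due to hormonal fluctuations associated with the menstrual cycle".

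**The concern.** The sham SD is one sixth of the active SD, and the section gives neither a reason nor a sensitivity range. Averaging 0.3 with 1.8 lowers the working SD from 1.8 to 1.290, a reduction of 28%, and the stated power depends on it. The value is hard to accept as a patient-level SD of change. These women enter with an average NRS of at least 4 and rate recalled pain, and rating noise and natural fluctuation act in both arms. Student's t-test also assumes a common variance, so a sixfold SD ratio fits poorly with the planned analysis.

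The effect size raises a second question. It implies a between-group difference of 1.25, a figure the text never states. On the text's own wording the expected active-minus-sham difference is 1.49.

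This paragraph is the article's only justification for the sample size. If the power is overstated, a non-significant result would be read as stronger evidence against the device than the design can supply.

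**Working it through.** **Inputs (Sample size calculation).** Total effect 1.73; true effect 1.49; placebo effect 0.24; SD 1.8 active and 0.3 sham; effect size 0.969; two-sided alpha 0.05; power 0.9; 24 per group.

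**Step 1: reproduce the plan's figures.**
- Placebo: 0.14 × 1.73 = 0.242, so 0.24. True effect: 1.73 − 0.24 = 1.49.
- Root-mean-square SD: √((1.8² + 0.3²)/2) = √((3.24 + 0.09)/2) = 1.290.
- Effect size: (1.49 − 0.24)/1.290 = 1.25/1.290 = 0.969, which matches. Using 1.49 would give 1.49/1.290 = 1.155, which does not.
- Sample size at 0.969 by the noncentral t distribution: 23.4, so 24 per group. Power at 24 is 90.8%. A simulation with SDs 1.8 and 0.3 and a difference of 1.25 gives 90.6% for Student's t.

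The calculation is therefore correct for its inputs.

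**Step 2: the difference.** The text says 1.73 contains both the true and the placebo effect. Active minus sham is then 1.73 − 0.24 = 1.49. Going on to 1.49 − 0.24 = 1.25 removes placebo twice. This lowers the assumed effect, so taken alone it is conservative.

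**Step 3: what a sham SD of 0.3 implies.** Under a normal model with mean change 0.24:
- 95% range: 0.24 ± 1.96 × 0.3 = −0.35 to +0.83.
- Proportion changing by a full point in the direction of the mean: P(Z > (1 − 0.24)/0.3) = P(Z > 2.53), about 0.6%.

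**Step 4: power over a range of sham SDs.** Noncentral t, 24 per group, active SD 1.8, effect size = difference/√((1.8² + sham SD²)/2):

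| Sham SD | Power, difference 1.25 | Power, difference 1.49 |
|---|---|---|
| 0.3 | 91% | 97% |
| 0.9 | 85% | 94% |
| 1.2 | 79% | 91% |
| 1.5 | 73% | 86% |
| 1.8 | 65% | 80% |

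Power falls below 90% once the sham SD exceeds about 0.42 (difference 1.25) or about 1.27 (difference 1.49).

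**Step 5: common SD of 1.8.**
- Effect sizes: 1.25/1.8 = 0.694 (power 65.4%) and 1.49/1.8 = 0.828 (power 80.2%).
- With 25 per group, all evaluable: 67% and 82%.
- Difference detectable with 90% power at 24 per group: 0.956 × 1.8 = 1.72, almost the whole total effect of 1.73 with placebo included.
- Number per group for 90% power: 45 (difference 1.25) or 32 (difference 1.49), before dropout.

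**The case against.** The strongest reply is that the document's own true effect is 1.49, and that for this difference power stays at or above 90% until the sham SD reaches about 1.27, roughly four times the stated value. This stands. A reader might infer that the trial has only 65 to 80% power, or a 20 to 35% chance of missing its planned effect. The documents do not support that as a general statement. It holds only at a sham SD of 1.8, which no section gives for the sham device, and the 65% also requires the doubly reduced difference of 1.25.

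It can also be said that SDs may truly differ if response to an active device varies between women, and that the source trial is not available here. Both are fair. They leave 0.3 unexplained in the text, but they mean that 1.8 for sham is an assumption and has to be shown within a range.

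Two supporting arguments carry little weight. If changes were recorded in whole points, a mean of 0.24 would force an SD of at least √(0.24 × 0.76) = 0.43. The visit score is described as an average over 4 weeks, however, so whole-point recording is not established, and 0.43 still gives 90.0% power at 1.25. The menstrual-cycle limitation in the Discussion gives no figure for the between-woman SD, and the 4-week recall probably smooths part of that variation.

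Finally, the word conservative has some basis, because using 1.25 in place of 1.49 is a cautious step. It does not describe the choice of SD.

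**Conclusion.** The concern holds as a fault in the inputs, not in the arithmetic. The 90% figure requires a sham SD of 0.3, which is unjustified and implausibly small as a patient-level SD of change, together with a difference of 1.25 that conflicts with the text's true effect of 1.49. The two faults pull in opposite directions and partly cancel.

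Over sham SDs from 0.3 to 1.8, power at 24 per group runs from 97% down to 80% for a difference of 1.49, and from 91% down to 65% for 1.25. The 65% is the pessimistic corner of that range and should not be quoted as the power of the trial. These figures assume an active SD of 1.8, normally distributed changes, 24 evaluable women per group and a two-sided 5% Student's t-test.

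**What to change.** Keep N = 50 and rewrite the sample size paragraph:

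1. State which between-group difference is intended (1.49 on the text's own wording, or 1.25 with a reason) and make the effect size match it.
2. Replace the sham SD of 0.3 with a common SD of 1.8 as the planning value, in line with Student's t-test, and label it an assumption. Show power over a range of sham SDs up to 1.8, as in the table above.
3. Restate the power accordingly. At a common SD of 1.8 and 24 per group it is about 80% for 1.49 and, as the pessimistic corner, about 65% for 1.25. The difference detectable with 90% power is 1.72.
4. Delete the word conservative, or limit it to the choice of difference.

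The cost is one paragraph of wording, with no extra participants and no change to endpoint or test. The downside is that the stated power becomes less favourable.
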